### Sample size

This study will enrol 418 patients to detect a difference in IPC-related infection rate between the treatment arms. The difference that we wish to detect is 10% in the topical mupirocin prophylaxis arm (i.e. a relative reduction in infection rates of 50%) *vs* 20% in the no topical mupirocin prophylaxis (standard care) arm (based on previous studies) [7, 15–18, 25]. Previous randomised clinical trials (RCTs) reported a pleural infection rate of ~ 10% [7, 25]. Incidences of tract infection and cellulitis (combined) are often similar to the pleural infection rates in published papers. Hence, we estimated a 20% incidence for overall IPC-related infections. In the RCTs investigating mupirocin prophylaxis in PD patients, a two-third reduction in infection rates (*vs* control arms) were commonly reported [15–17]. To be conservative, we therefore estimated an incidence of 10% in our treatment arm. The sample size calculation was carried out using an anticipated chi square test to compare these proportions, assuming a 5% significance level and a power of 80%. To achieve this, we would need 199 patients per group (with an additional 5% to allow for dropouts based on previous AMPLE trial [6]), giving a total of 418 patients.

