### Randomisation

Participants will be randomised 1:1 to either topical mupirocin or no topical mupirocin (standard care). Randomisation will include minimisation for (i) cancer type (mesothelioma *vs* non-mesothelioma), (ii) known presence of trapped lung (*vs* not), (iii) ECOG performance status (≤ 2 *vs* ≥ 3), and (iv) current immunosuppression (or chemotherapy) *vs* not. The Griffith Randomisation Service by the Griffith University, Queensland, Australia, provides the randomisation setup via their automated web portal. The site principal investigator or designated site research staff screening patients will be able to generate the allocation sequence using the automated centralised randomisation system, enrol participants, and assign participants to interventions based on the randomisation.

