### Statistical plan

Data will be analysed on an intention-to-treat basis and per protocol basis. All participants, excluding those who withdrew prior to the randomisation intervention, will be included in the intention-to-treat analyses and analysed according to their randomised assignment. Per-protocol analyses will be performed in participants who have had at least one week of mupirocin application *vs* those who did not have any. Sensitivity analysis, e.g. with multiple imputation, will be carried out whenever appropriate, to account for missing data. The primary outcome will be analysed using chi-square test and subsequent logistic regression analyses allowing adjustments for minimisation variables. A secondary analysis of the primary outcome will utilise the time to event data, where cumulative incidence plots will be presented, and the log-rank statistic used to compare the treatment groups. In addition, Cox regression models will be used to calculate cause specific hazard ratios adjusted for minimisation variables. A competing risk analysis will also be performed to account for the competing risk of death in estimation of event rates. For binary or continuous secondary outcomes, inter-group differences will be examined using chi-square tests or two sample *t*-tests respectively, with additional logistic and linear regression analyses adjusting for minimisation variables. Adverse and serious adverse events will be reported in descriptive figures. Data analysts will be masked to the assigned groups, where appropriate.

An interim analysis is planned after 100 patients have been enrolled and completed follow-up. The purpose is to (i) assess the rate of recruitment and determine the feasibility of fulfilling the enrolment target and (ii) futility—observe the actual incidence of event rates in the control group to ensure the study is adequately powered to detect a clinically meaningful difference. We would determine if the conditional power based on the trend observed at the interim analysis decreases to less than 0.2. The need for further interim analysis will be assessed accordingly, and any decision to terminate the trial will be made by the trial steering committee.

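### The futility threshold at 100 patients, if followed, would flag a trial with the planned effect as futile about 21–22% of the time and lower power to about 68–70%, and the 80% power calculation makes no allowance for it

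*Protocol article*

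**What the plan says.** The Statistical plan section of the protocol article fixes the time of the look: "An interim analysis is planned after 100 patients have been enrolled and completed follow-up". It gives two purposes, feasibility of recruitment and futility. Futility is introduced as a check on the control-group event rate, and the criterion follows: "We would determine if the conditional power based on the trend observed at the interim analysis decreases to less than 0.2". The section does not say what happens when the value is below 0.2. It leaves open whether further looks are needed and gives any termination decision to the trial steering committee. The Abstract makes recruitment up to 418 conditional on interim analyses.

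The Sample size section describes a single-stage comparison. "The difference that we wish to detect is 10% in the topical mupirocin prophylaxis arm", against "20% in the no topical mupirocin prophylaxis (standard care) arm". The calculation is for a chi-square test, "assuming a 5% significance level and a power of 80" per cent, and gives "we would need 199 patients per group". The only inflation is 5% for dropouts, to 418 in total.

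**The concern.** Timing, metric and threshold are all stated, so their operating characteristics can be worked out. At 100 patients with 1:1 allocation, the planned rates imply about 10 infections in the control arm and 5 in the mupirocin arm. Conditional power under the observed trend extrapolates that small difference over the remaining three quarters of the trial, so chance variation of a few infections moves it a long way. A trial in which mupirocin halves the infection rate, exactly as planned, can easily fall below 0.2.

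The 80% power was calculated as if no such look existed. If the committee acts on the threshold, a useful prophylaxis may be abandoned, and the chance of showing the planned effect is lower than the article states.

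**Working it through.** **Inputs.** Sample size section: 20% vs 10%, 5% significance, 80% power, chi-square test, 199 per group, 418 in total. Randomisation section: 1:1. Statistical plan section: look at 100 patients, conditional power (CP) under the observed trend, threshold 0.2. Assumptions: two-sided 5% (the article does not state sidedness, but this reproduces its figure), 50 patients per arm at the look, no efficacy stopping.

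**1. The plan's own figure.** n = [1.960·√(2·0.15·0.85) + 0.8416·√(0.2·0.8 + 0.1·0.9)]² / 0.1² = (0.9897 + 0.4208)² / 0.01 = 198.97, so 199 per group. 398 × 1.05 = 417.9, so 418. The stated sample size is reproduced. Power without a look is 80.0% with 199 per arm and 81.9% with 209 per arm (normal approximation).

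**2. What CP < 0.2 means at the look.** With information fraction t and interim statistic z,
CP = Φ[(z/√t − 1.960)/√(1 − t)].
CP < 0.2 is therefore z < √t·[1.960 − 0.8416·√(1 − t)].
- 199 per arm: t = 100/398 = 0.251, cut-off 0.5013 × (1.960 − 0.8416 × 0.8653) = 0.617.
- 209 per arm: t = 100/418 = 0.239, cut-off 0.4891 × (1.960 − 0.8416 × 0.8722) = 0.600.

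In counts, 10 vs 8 infections gives z = 0.52 and CP of 0.14–0.15 (below the threshold). 10 vs 7 gives z = 0.80 and CP of 0.34–0.35 (above it). One infection decides.

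**3. Chance of a flag under the planned effect.** The expected interim z is drift × √t.
- 199 per arm: 2.802 × 0.5013 = 1.404; Φ(0.617 − 1.404) = 21.6%.
- 209 per arm: 2.872 × 0.4891 = 1.405; Φ(0.600 − 1.405) = 21.0%.

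**4. Power if every flag leads to a stop.** The bivariate normal calculation gives 67.6% (199 per arm) and 69.1% (209 per arm). Exact binomial enumeration, with the uncorrected chi-square test at the end, gives:

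| Final n per arm | Flagged at 20% vs 10% | Power, no look | Power, threshold always followed | Loss |
|---|---|---|---|---|
| 199 | 22.4% | 80.9% | 67.6% | 13.2 points |
| 209 | 20.8% | 82.5% | 69.7% | 12.8 points |

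The loss is smaller than the flag rate because only 59–61% of the flagged trials would have ended significant.

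**5. Sensitivity to convention.** If CP also counts a significant result in the wrong direction, the flag rate is 18.6–20.5%.

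**6. Alternatives, at 20% vs 10% and under no effect.** For CP under the design effect, the remaining data are assumed to follow 20% vs 10%: CP = Φ[(z√t + θ(1 − t) − 1.960)/√(1 − t)], with θ the design drift.

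| Rule (CP < 0.2) | Effective trials flagged | Power lost if followed | Null trials flagged |
|---|---|---|---|
| Observed trend, 100 patients (as written) | 21–22% | about 13 points | about 73% |
| Observed trend, about half the patients | 14–15% | about 6 points | about 83% |
| Design effect, 100 patients | about 0.1% | negligible | about 3–5% |
| Design effect, about half the patients | 1.6–1.8% | about 0.2 points | about 47% |

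Moving the look without changing the metric does not remove the problem. Changing the metric without moving the look leaves a test that almost never flags anything.

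**The case against.** The strongest objection is that the article does not commit to stopping. It says the team would determine whether conditional power is below 0.2, allows for further looks, and leaves termination to the trial steering committee, which also reviews recommendations from a data and safety monitoring board with an independent statistician. A reader might infer from the threshold that the rule does stop one effective trial in five and that the stated 80% power is not delivered. The document does not support that: 68–70% is the floor, reached only if every flag is acted on. This part of the objection stands in full.

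It does not remove the point. A futility threshold is there to be acted on, and its being non-binding protects the type I error, not the power. The article gives the committee no ground for overriding a flag that the planned effect itself produces about one time in five.

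Three further arguments have some weight. First, futility is introduced through the control-group event rate. The criterion attached to it is nevertheless conditional power under the observed trend, and the natural reading of that is the between-arm comparison. Second, the early observed-trend rule has a merit: it flags about 73% of null trials. How much power to give up for early stopping is a design choice, but the choice should show in the stated power. Third, whether the threshold is binding and who computes it may be set out in an analysis plan or charter that is not shown. The point does not depend on that, because the timing, metric, threshold and power claim all stand in the article.

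**Conclusion.** The concern holds in conditional form. The sample size arithmetic is correct for a fixed design, and a futility-only look does not inflate the type I error. But the look as specified does not fit the power claim. If the threshold is followed, a trial with the planned effect is flagged about 21–22% of the time and power is about 68–70%, a loss of about 13 points. Actual power lies between that and about 81–82%, depending on how often the committee acts on a flag. The article does not establish that 80% power will be missed. It sets a criterion that would cause this if applied, and the power statement does not account for it.

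The figures rest on a two-sided 5% test, 50 patients per arm at the look, true rates of 20% and 10%, and conditional power counted in the favourable direction.

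**What to change.** In the Statistical plan section:

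- Keep the look at 100 patients for recruitment and event rate only.
- Test futility when about half the patients have completed follow-up, with conditional power computed under the design effect (20% vs 10%). The 0.2 threshold can stay.
- State that the threshold is non-binding.

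If the present rule is kept instead, state in the Sample size section that power is about 68–70% when it is followed.

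The change is a short amendment with no increase in sample size, but it has a cost. A truly ineffective trial would be stopped later and less often: about 47% of null trials at half information, against about 73% at 100 patients now. As a rough guide, assume uniform accrual of 418 patients from 21.07.23 to the end of March 2026 (about 32.3 months, 12.9 a month) and 6 months of follow-up. About 100 + 78 = 178 patients would then be enrolled when 100 have completed follow-up, and about 209 + 78 = 287 when 209 have. The amendment should be made before anyone sees comparative interim data, since a rule changed afterwards would carry little weight.

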### Ethics

The trial has been approved (as of 20 December 2023) by the following committees:Sir Charles Gairdner Osborne Park Healthcare Group Human Research Ethics Committee (HREC) for Australian public hospitals, AustraliaSt John of God Health Care Ethics Committee for Midland Hospital, Western AustraliaUniversiti Kebangsaan Malaysia Research Ethics Committee for University Kebangsaan Malaysia Medical Centre, MalaysiaNorthern B Health and Disability Ethics Committee for hospitals in New ZealandMacquarie University Human Research Ethics Committee, Medical Sciences, Australia

Study investigators will ensure that any amendments to the protocol is approved by the ethics committee and signed by any patients subsequently entering into the trial and those currently in the study, if affected by the amendment.

### Trial monitoring and oversight

The trial steering committee (TSC) will be responsible for the supervision of the trial in all its aspects. It will be responsible for ensuring the completion of the trial to clinical and ethical standards. Members of the TSC include an independent chairperson, independent member(s), chief investigator and selected investigators, a consumer representative, and the trial coordinator(s). The TSC will monitor site recruitment and review any recommendations received from the data and safety monitoring board (DSMB). The DSMB ensures the safety of study participants through monitoring of ethical conduct of the study and study procedures, reviewing adverse events, and considering new data (recently published studies) that may determine the validity of study continuation. The DSMB includes an independent chairperson and other independent members, one of whom is a statistician.

### Adverse events

All adverse events relating to the study, serious and non-serious, will be fully documented according to the ‘Adverse Event Reporting’ Section of the Investigator Site File. An adverse event is defined as any untoward medical occurrence, including an exacerbation of a pre-existing condition in a patient in a clinical investigation who received an experimental procedure. The event does not necessarily have to have a causal relationship with this treatment. A serious adverse event is defined as any adverse event/adverse reaction that results in death, is life-threatening, requires hospitalisation or prolongation of existing hospitalisation, and results in persistent or significant disability of incapacity.

All adverse events relating to and occurring during the course of the clinical study (i.e. from signing the informed consent until death or the end of the study follow-up period, whichever comes first) will be collected, documented, and reported to the DSMB. Events will also be reported if a causal link (relatedness) between the adverse event and the study is suspected but not confirmed.

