### Monitoring and follow-up

Potential participants, as part of the informed consent process, will have the study procedures and follow-up plan discussed in detail.

All patients (or their carers/nurses) will be contacted by phone every week to assess for clinical outcomes, compliance, or adverse events until death or end of 6-month follow-up period (Table 1). Frequency of the phone review will decrease to monthly once the IPC is removed. If the patient is attending hospital visits for other reasons, then the telephone review may be replaced by face-to-face assessment.

**Table 1 Tab1:** Schedule of treatment for each visit and follow-up procedures

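### The adverse-event rules contradict each other and the all-patient review, and could lead to events being recorded differently in the two arms

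*Protocol article*

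**What the plan says.** The Adverse events section of the protocol article contains these rules:

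- **Who can have an event.** The occurrence must arise "in a patient in a clinical investigation who received an experimental procedure".
- **Causality.** "The event does not necessarily have to have a causal relationship with this treatment".
- **Documentation.** "All adverse events relating to the study, serious and non-serious, will be fully documented", with details left to the Investigator Site File.
- **Collection.** "All adverse events relating to and occurring during the course of the clinical study" are collected and reported to the DSMB. The window is given as "from signing the informed consent until death or the end of the study follow-up period, whichever comes first".
- **Suspected relatedness.** "Events will also be reported if a causal link (relatedness) between the adverse event and the study is suspected but not confirmed".
- **Serious events.** The list runs through death and threat to life and ends: "requires hospitalisation or prolongation of existing hospitalisation, and results in persistent or significant disability of incapacity".

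Other sections bear on this. Under Monitoring and follow-up, all patients (or their carers or nurses) "will be contacted by phone every week to assess for clinical outcomes, compliance, or adverse events", falling to monthly once the catheter is out. Table 1 schedules an adverse event review at day 1 and weeks 1–24 without separating the arms. Secondary endpoints lists adverse and serious adverse events, without restriction by arm, and sends the reader to the adverse events section for the definitions. The Statistical plan reports them descriptively. Controls have usual catheter care without mupirocin.

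**The concern.** A safety outcome can be compared between arms only if the same kind of event is counted in each. Two features of the text put that in doubt. The definition is tied to receiving something experimental, and mupirocin, the only treatment that differs by allocation, is given in one arm. Entry into the record also appears to depend on a link to the study. Staff know the allocation, and controls receive no study drug to which an event could be attributed.

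At stake is how the adverse-event tables are read, both by the DSMB during the trial and in the final report. A higher count under mupirocin could be a real effect, such as local reactions, or a product of the entry rule. The tables could not tell these apart.

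**Working it through.** The document gives no adverse-event figure to reproduce, so most of the check sets the text side by side.

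**1. Who is covered.** The sentence after the definition speaks of the treatment, which suggests that the experimental procedure is the study treatment. Catheter insertion does not fit that description: patients enter because they need a catheter (Inclusion criteria), and catheter care follows local standard practice whatever the allocation (Clinical care). On this natural reading controls are not clearly included. But collection opens at consent, before anyone in either arm has received anything. The definition and the window therefore do not match.

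**2. Whether relatedness is required.** The documentation and collection sentences both carry a relatedness qualifier. The final sentence says that events of suspected relatedness will *also* be reported. That word adds something only if the preceding rule requires a causal link. The definition says that no such link is needed. Sites cannot follow both.

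**3. Whether equal contact cures this.** The weekly calls and Table 1 fix when staff ask, in both arms. They do not fix which answers become a recorded event. For that, Secondary endpoints refers back to the section in question.

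**4. Serious events.** Joined by *and*, the criteria read literally as cumulative, so that death would count only together with hospitalisation and lasting disability.

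**5. Size.** The arm size follows from Sample size: 199 × 1.05 = 208.95, rounded up to 209 per arm, and 2 × 209 = 418. The rest is illustration under assumptions that are not in the document: the true risk *p* of a recordable event is equal in both arms, the mupirocin arm records all its events, and the control arm records a fraction *f*.

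- Apparent risk ratio = *p* / (*p* × *f*) = 1/*f*
- Spurious risk difference = *p* × (1 − *f*)

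| *f* | Apparent risk ratio | Spurious difference, *p* = 10% to 30% |
|---|---|---|
| 1.00 | 1.0 | 0 |
| 0.75 | 1/0.75 = 1.33 | 2.5 to 7.5 points |
| 0.50 | 1/0.50 = 2.0 | 5 to 15 points |
| 0.25 | 1/0.25 = 4.0 | 7.5 to 22.5 points |

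For example, with *p* = 20% and *f* = 0.5, the mupirocin arm would show 209 × 0.20 = 41.8 expected patients with an event, and the control arm 41.8 × 0.5 = 20.9. Nothing in the document says what *f* would be, and it may be 1. The table shows direction and sensitivity only.

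**The case against.** The strongest reply is that this is loose wording in a condensed article. All patients are asked about adverse events on the same schedule, and the secondary endpoint has no arm restriction. The experimental procedure is undefined and could mean any study procedure. In the collection sentence, the qualifier is followed at once by a time window, so it may be meant only as a period. The operational rules sit in the Investigator Site File and in the practice of earlier trials in the series, neither of which is shown. No site would require death plus disability before calling an event serious.

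Much of this stands. The exclusion of controls is one reading of an ambiguous term. The *and* is a drafting slip that sites would read as *or*. The time-window reading of the collection sentence is fair, but it does not explain the documentation sentence, which has no window, or the separate provision for suspected relatedness. Better wording in the site file would not remove the contradiction in the published text.

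A reader might go further and infer that the control arm contributes almost nothing to the safety data. The documents do not support that. It would need *f* near 0, which conflicts with the scheduled review of every patient. Nor are 209 of 418 patients shown to be lost to safety recording: 209 is simply the size of one arm.

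**Conclusion.** The adverse-event rules are inconsistent with each other and with the all-patient review, and should be reconciled. As they stand, a descriptive difference between arms could partly reflect differential recording. The likely direction is towards more events in the mupirocin arm. The size cannot be computed from the document.

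This rests on two assumptions: that sites apply the published wording, and that in an open-label trial against no treatment an event is more readily linked to the study when a study drug is being used.

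The reach is limited. A reader might infer that any excess under mupirocin is an artefact, but real local reactions are possible and the text cannot settle the matter. Nor is a formal safety comparison at risk, since the Statistical plan states only descriptive reporting for adverse events. Deaths, hospital days for any reason and catheter-related infections are collected in both arms under Primary endpoint and Secondary endpoints, independently of these definitions. The primary analysis and the sample size are unaffected.

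**What to change.** - Define an adverse event as any untoward medical occurrence in any randomised participant, in either arm, whether or not it is thought to be related.
- Apply one recording rule to both arms at the reviews already in Table 1.
- Record relatedness as an attribute of each event, and remove it as a condition of entry.
- If the load in advanced cancer must be limited, fix one list of non-serious events in advance and use it for both arms.
- Replace *and* by *or* in the serious-event criteria.
- Check the Investigator Site File against the revised text. If it already has an arm-neutral rule, bring the protocol wording into line with it.

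The cost is a wording amendment and some extra event forms, mainly in the control arm. No new contacts are needed. Because recruitment began in July 2023, the report should state the date of the change and whether earlier events were recorded under the same rule.

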#### No topical mupirocin (standard care) arm

Patients assigned to the standard care arm will be managed in the conventional manner with the usual education and care of the IPC and without topical mupirocin prophylaxis.

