### Secondary endpoints

Infection will be analysed:As the total number of episodes for all patients in each group;As percentage of patients and as total number of episodes—each adjusted for number of days IPC is in situ for each patient;As each of the individual types of infection;Time to first episode of infection; andFor organism(s) causing infection (e.g. *S. aureus **vs *others)Hospital days will be analysed:As total days in hospital (for any reasons)As days related to IPC-related infections, similar to methods used in prior AMPLE trials [6, 25]. All records of hospitalisation will be reviewed by an independent investigator.Adverse and serious adverse events will be recorded as in previous AMPLE trials [6, 25]. Definitions for adverse and serious adverse events are listed under adverse events section in the protocol.Resources used associated with antibiotics use and IPC-related infections will be obtained from discharge letters and hospital in-patient enquiry coding. In-/out-patient management of any related complications will be captured from hospital records or self-reports from patients and will include treatments, imaging, and other interventions related to the adverse events. An experienced health economist will oversee this study aspect.Survival will be measured from randomisation to death or end of study follow-up.

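### The adverse event section contradicts itself, and its relatedness filter risks unequal capture of adverse events between the arms

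*Protocol article*

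**What the plan says.** The Adverse events section of the protocol article defines an adverse event as an untoward occurrence in "a patient in a clinical investigation who received an experimental procedure". It does not say what the experimental procedure is. The definition continues: "The event does not necessarily have to have a causal relationship with this treatment". Serious adverse events are those adverse events or reactions that meet a seriousness criterion, so they inherit the definition.

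The section then states what is captured, in two places. On documentation: "All adverse events relating to the study, serious and non-serious, will be fully documented". On collection and reporting to the DSMB: "All adverse events relating to and occurring during the course of the clinical study", with a window that runs "from signing the informed consent until death or the end of the study follow-up period, whichever comes first". It adds: "Events will also be reported if a causal link (relatedness) between the adverse event and the study is suspected but not confirmed".

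Other sections bear on the same point:

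- **Secondary endpoints** lists adverse and serious adverse events with no restriction by arm, and refers back: "Definitions for adverse and serious adverse events are listed under adverse events section in the protocol".
- **Monitoring and follow-up** has every patient, or a carer or nurse, phoned weekly (monthly once the catheter is out), with adverse events among the items asked about. Table 1 places adverse event review at day 1 and weeks 1–24, with no split by arm.
- **No topical mupirocin (standard care) arm** has control patients managed conventionally, "without topical mupirocin prophylaxis".
- **Study design** describes the trial as open-label, and **Statistical plan** has adverse events reported descriptively.

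**The concern.** Adverse events are a secondary outcome and part of what the DSMB reviews. Comparing them by arm requires that the same event has the same chance of being recorded in each arm. Two features of the section put that at risk.

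First, the definition depends on having received something that is not specified, and on one reading only half of the participants receive it. Second, an event enters the record only if someone judges that it relates to the study, or suspects so. Those who judge know the allocation, and one arm has a study product to blame while the other has usual care.

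If capture differs between the arms, a difference in the safety figures may reflect attribution rather than harm. It could suggest an excess on mupirocin that is not real. An event judged unrelated would also be lost from both arms, where a true imbalance could go unseen.

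**Working it through.** No figure in the documents can be reproduced on this point: no adverse event rate is given for either arm. The check is a comparison of the texts.

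**1. What the experimental procedure could mean**

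| Reading | Support in the article | Consequence |
|---|---|---|
| Mupirocin application | It is the only randomised treatment; the Background presents the indwelling pleural catheter (IPC) as an established first-line option; the Inclusion criteria take patients who already need one; the definition goes on to speak of a treatment | Control patients, 418 / 2 = 209 as planned, fall outside the definition |
| IPC insertion | Table 1 uses the word procedure for the insertion at day 0 and lists mupirocin under interventions | Both arms are covered once the catheter is in |

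The article does not choose. The first reading conflicts with Monitoring and follow-up, Table 1 and Secondary endpoints, all of which cover every patient. The second agrees with them but calls an established procedure experimental.

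**2. Definition against window**

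Table 1 puts consent at enrolment and catheter insertion at day 0, after it. The window opens at consent. Under either reading there is a period, from consent to the procedure, in which the window is open but nothing can meet the definition.

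**3. Definition against capture rule**

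The definition requires no causal relationship. The capture rule keeps events that relate to the study. The added sentence on suspected links indicates that the rule works as a relatedness filter: it would be redundant if every event were collected. The filter is therefore one of confirmed or suspected relatedness, and it applies to documentation, collection and DSMB reporting.

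**4. Effect of the filter on a comparison by arm**

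Let *p* be the true event rate, taken as equal in the two arms, and let *q*_M and *q*_C be the probabilities that staff judge an event in the mupirocin and control arms to relate, or possibly relate, to the study. Then:

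- recorded rate, mupirocin = *p* × *q*_M
- recorded rate, control = *p* × *q*_C
- recorded ratio = *q*_M / *q*_C, although the true ratio is 1

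The comparison is fair only if *q*_M = *q*_C. With open allocation and a usual-care control, *q*_M > *q*_C is plausible, for example for a skin reaction at the exit site. The documents give neither value, so the direction can be argued but the size cannot be computed.

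**5. What does not pass through the filter**

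Survival is measured from randomisation, and total hospital days are counted for any reason (Secondary endpoints). The primary endpoint has its own infection definitions. None of these depends on the adverse event definition. The exposed information is mainly non-serious events, the causes of serious ones, and the DSMB's event listings.

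**The case against.** A reader might infer that the control arm would have almost no adverse events by construction, that control-arm deaths would go uncounted while those on mupirocin were counted, and that the safety comparison is void. The documents do not support this, for these reasons:

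- The inference needs the mupirocin-only reading. Table 1 uses procedure for the catheter insertion, which both arms undergo, and the window opens before any mupirocin.
- All patients are asked about adverse events on the same schedule, so the intent to cover both arms is plain.
- The filter refers to the study, not to mupirocin, and suspected links count. Catheter problems can be reported in either arm.
- Counting lost control deaths ignores the filter itself. A death from advanced cancer that nobody links to the study would be left out in both arms, and survival captures it in both.
- Analysis is descriptive, so no formal safety test is at stake.

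All of this stands against the strong reading. It does not remove the narrower point. The common schedule fixes when staff ask, not what counts, and Secondary endpoints sends the reader to the Adverse events section for the definitions. Descriptive figures by arm can still mislead if capture differs.

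It is also fair that operational detail may sit in the full protocol or in the Investigator Site File section that the article cites, neither of which is shown. Either may settle the scope. But the article does more than omit detail: it prints a definition and a capture rule that do not agree with each other.

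**Conclusion.** The point holds as a moderate defect of wording with a real risk attached. The Adverse events section cannot be followed as written: its definition, window and capture rule disagree, and one reading of the definition conflicts with the sections that cover all patients. Under the relatedness filter, unblinded attribution decides which events enter a secondary outcome and the DSMB listings, so those may not be comparable between the arms.

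The conclusion assumes that sites apply the section as printed and that knowledge of allocation influences attribution. No number can be put on the effect from these documents. The primary endpoint, survival and all-cause hospital days are not affected.

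**What to change.** Reconcile the Adverse events section with Monitoring and follow-up, Table 1 and Secondary endpoints:

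1. Define an adverse event as any untoward medical occurrence in any enrolled participant, in either arm, over the window already stated (consent to death or end of follow-up). Remove the reference to an experimental procedure.
2. Remove *relating to* as a condition for documentation, collection and DSMB reporting, at minimum for all serious events. If a filter is kept for non-serious events, define it identically for both arms.
3. Record relatedness as an attribute of each event.
4. Ask about events in the same words in both arms at the contacts already scheduled.

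This costs one paragraph in an amendment and a line on the case report form, with no extra visits. The downside is somewhat more event recording in both arms. Recruitment began in July 2023, so the report should state from what date the revised scope applied.
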